**Methods:**

People who have experienced a cardiac event in the previous 12 months and have access to the internet will be eligible for this study (N=120). Participants will be randomly assigned to one of the two study conditions: either “self-directed” completion of the *Back on Track* program (without assistance) or “supported” completion of the *Back on Track* program (additional 2 telephone sessions with a lifestyle counselor). All participants will have access to the web-based *Back on Track* program for 2 months. Telephone sessions with the supported arm participants will occur at approximately 2 and 6 weeks post enrollment. Measures will be assessed at baseline, and then 2 and 6 months later. Outcome measures assessed at all 3 timepoints include dietary intake, physical activity and sitting time, smoking status, anxiety and depression, stage of change, and self-efficacy in relation to behavioral and emotional self-management, quality of life, and self-rated health and well-being. A demographic questionnaire will be included at baseline only and program acceptability at 2 months only.

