#### Additional Telephone Sessions for the Supported Group

Supported group participants are offered 2 telephone sessions with a trained lifestyle counselor to assist them in goal-setting and overall self-management while undertaking program modules. The session duration is 45-60 minutes for session 1 and up to 30 minutes for session 2. The first session occurs around 1-2 weeks postenrollment. The counselor begins the session with rapport development, then screens for anxiety and depression using the Patient Health Questionnaire-4 (PHQ-4) [53]. Self-efficacy for managing changes associated with health behaviors and emotional well-being is also assessed. Decisional balance and ambivalence are explored.

Motivational interviewing strategies are used to support participants to articulate clear and achievable goals and to identify areas they wish to address in behavioral and emotional self-management. Action and coping planning interventions are used to support translation of goals into actions. At completion of the first session, the second telephone session is scheduled for a mutually agreed time (approximately 4 weeks after the first session). The second telephone session includes a reflection on anxiety or depression symptoms, self-efficacy, coping and action plans, relapse prevention, and maintenance of behaviors. In addition, if the counselor considers that the individual requires more intensive mental health support, referral options for counseling are discussed.

An SMS reminder is sent 24 hours prior to each telephone session appointment to facilitate engagement. To ensure consistency and quality of program delivery, lifestyle counselors receive fortnightly supervision with an experienced registered health psychologist.

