### Measures

Sociodemographic information is collected at baseline only. All participants complete the outcome measures of dietary intake, physical activity and sitting time, smoking status, anxiety and depression, stage of change, and self-efficacy in relation to behavioral and emotional self-management, quality of life, self-rated health, and well-being at baseline, post program (2 months after initial access to the program), and at 4-month follow-up (6 months after program access). Program acceptability is assessed post program only using a 6-item scale developed specifically for this study.

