### Data Analysis

In evaluating outcomes, there will be two groups of participants based on the mode of delivery: “self-directed” and “supported.” All statistical analyses will be performed on an intention-to-treat (ITT) basis with *P*<.05. In the case that ITT produces a null finding, it is possible that this is due to participants in the supported group not participating in the additional telephone sessions (that is, not receiving the intended treatment). To test that hypothesis, we will then undertake treatment-received analysis (also called Per Protocol) whereby only those who received the treatment in accordance with the protocol are included. This will enable us to determine whether any differences were obtained between those who received the self-directed treatment and those who received the supported treatment. *P* values less than .05 will be considered significant for the primary outcome and those less than .01 will be considered significant for secondary outcomes. The effect of the intervention on the primary and secondary outcomes at 6 months will be assessed using analysis of covariance (ANCOVA) models that include the baseline value of the outcome as a covariate and the group assignment (self-directed versus supported) as a categorical variable. The treatment effect, its effect size (Hedge g), and 95% CIs for the treatment effect and within-group changes from baseline to 6 months will be calculated from the ANCOVA models. The sensitivity of the results to missing data will be evaluated using a data-based multiple imputation procedure.

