### Primary Outcome Measures: Depression, Physical Activity, and Dietary Intake

As the main outcomes, we will examine differences between the 2 groups in the proportion of participants who are:

classified as *nondepressed* at baseline, post program, and follow-up (based on a PHQ-9 score of <6) [55,56],achieving physical activity guidelines of ≥150 minutes of physical activity per week [52] at baseline, post program, and follow-up, orachieving healthy dietary guidelines of DQT scores >60% [62] at baseline, post program, and follow-up.

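### Labelled intention-to-treat, the 6-month ANCOVA in effect analyses only 6-month responders and can be biased if dropout differs between arms

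*Protocol article*

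**What the plan says.** All of the following is in the Data Analysis section of the protocol article unless noted.

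- Population: "All statistical analyses will be performed on an intention-to-treat (ITT) basis".
- Model and time point: "The effect of the intervention on the primary and secondary outcomes at 6 months will be assessed using analysis of covariance (ANCOVA) models".
- Terms in the model: they "include the baseline value of the outcome as a covariate and the group assignment (self-directed versus supported) as a categorical variable". The 2-month score is not among them.
- Missing data: "The sensitivity of the results to missing data will be evaluated using a data-based multiple imputation procedure". No other rule is given for a participant without a 6-month score.
- The treatment effect, its effect size and interval, and the within-group changes to 6 months all come from these ANCOVA models.

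The 2-month outcomes exist. The abstract's Methods paragraph says "Measures will be assessed at baseline, and then 2 and 6 months later", and the Measures section confirms that the outcome set is repeated at each visit.

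**The concern.** An ANCOVA of a 6-month score needs a 6-month score. If imputation is only a check on that model, the headline estimate comes from 6-month responders. Someone who answers at 2 months and then stops is left out of it, although the 2-month answer is probably the best available predictor of the missing value. That does not fit the intention-to-treat label.

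Two results depend on it. The first is the supported versus self-directed difference, which is meant to inform how the program is rolled out. The second is the improvement within each arm, which the Objectives section states as the first hypothesis. If those who leave are doing worse than those who stay, each arm's responders look better than the arm as a whole. Whether this cancels in the between-arm difference depends on whether dropout works the same way in both arms.

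**Working it through.** **1. The plan's own sample size (Sample Size and Power).** Inputs: effect size 0.55, power 80%, alpha .05 (two-sided assumed), attrition 12%.
n per arm = 2 × (1.960 + 0.842)² / 0.55² = 51.9, so 52. With attrition, 52 / 0.88 = 59.1, so 60 per arm and 120 in total. The stated figure reproduces. The plan therefore expects 0.12 × 120 = 14.4, about 14 people, without an endpoint. The 12% comes from studies with post-tests at 2 to 4 months, whereas the ANCOVA is at 6 months, so a higher loss is possible. I use 25% as an assumed upper case.

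**2. Between-arm bias.** Large-sample simulation (400,000 records). Assumptions, none of them from the protocol: a continuous score with SD 1, higher meaning worse; correlation 0.5 between baseline and each later visit, and 0.7 between 2 and 6 months; logistic dropout with log-odds rising by 1 per SD of worse score. Dropout depends either on the observed 2-month score (A) or on the unseen 6-month score (B). The absolute bias of the 6-month difference, in SD, is:

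| Dropout | Completer ANCOVA, A / B | Imputed by arm with 2-month score, A / B |
|---|---|---|
| 12% in each arm, same mechanism | 0.00 / 0.00 | 0.00 / 0.00 |
| 12% in each arm, worse scorers leave one arm only | 0.05 / 0.08 | 0.00 / 0.055 |
| 18% v 6%, worse scorers leave both arms | 0.05 / 0.08 | 0.00 / 0.05 |
| 25% in each arm, worse scorers leave one arm only | 0.095 / 0.17 | 0.00 / 0.11 |

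Imputing from baseline alone, without the 2-month score, removed none of the bias.

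Sign: if the self-directed arm loses its worse scorers, the benefit of support is understated; if the supported arm does, it is overstated. With a true effect of 0.55 and 12% loss, the estimate was 0.50 in the first case and 0.60 in the second under A.

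**3. Size relative to precision.** At 12% loss, about 53 per arm: SE = √(2 × (1 − 0.5²) / 53) = 0.168. A bias of 0.05 to 0.08 is 0.30 to 0.48 SE. With no true effect, the two-sided 5% error rate becomes P(|Z + 0.30| > 1.96) = 6.0% to P(|Z + 0.48| > 1.96) = 7.6%. As a share of the planning effect, 0.05 / 0.55 = 9% and 0.08 / 0.55 = 15%. At 25% loss, 45 per arm: SE = √(2 × 0.75 / 45) = 0.183, so 0.095 to 0.17 is about 0.5 to 0.9 SE.

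**4. Within-group change.** Same assumptions, no true change, 12% dropout with the same mechanism in both arms (1,000,000 records). The completer ANCOVA, evaluated at the full-sample baseline mean, shows a spurious improvement of 0.05 SD (A) or 0.08 SD (B). The completers' raw change shows 0.02 or 0.055 SD. Imputation with the 2-month score gives 0.00 under A and 0.055 under B.

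**5. What the 2-month score cannot repair.** If leavers are δ SD worse than their earlier scores predict, each arm's mean is off by δ × its fraction missing. For example, with δ = 0.5 and 25% v 10% missing, 0.5 × (0.25 − 0.10) = 0.075 SD remains in the difference.

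**The case against.** The case on the other side has real force.

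- **The responder-only set is inferred.** The article never says complete-case. Imputation variables and similar detail are normally left to a statistical analysis plan, and their absence is no finding. What stands is the ordering that the article itself fixes: a baseline-and-group ANCOVA for the estimate, imputation only as a check, and no other rule for missing scores. On that wording a person without a 6-month score has nothing to enter.
- **Bias does not follow automatically.** A reader might infer that informative withdrawal by itself distorts the between-arm result. The first row of the table shows that it does not when rate and mechanism match across arms.
- **The documents do not show that dropout will differ.** A reader might take "An SMS reminder is sent 24 hours prior to each telephone session appointment to facilitate engagement" as better retention in the supported arm. Those messages concern counselling calls, which fall at about 2 and 6 weeks; questionnaire links are emailed to both arms. The Background remark on depressed mood concerns changing behaviour, not answering surveys, and would apply to both arms. Unequal contact makes different dropout possible, no more.
- **The direction may be conservative.** If it is the self-directed arm that loses its worse scorers, the error works against the claim that support is superior.
- **The 2-month data are not discarded.** The main outcomes are also compared "at baseline, post program, and follow-up (based on a PHQ-9 score of <6"), and several secondary scales have a repeated-measures analysis. But nothing says that these data inform the 6-month effect. The planned imputation might use them and so reveal part of the problem.
- **The main outcomes are proportions.** The simulation is of a continuous score, so its SD figures do not translate directly into differences in proportions.

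**Conclusion.** The point holds in conditional form. As written, the 6-month ANCOVA is in effect a completer analysis under an intention-to-treat label, and it leaves dropouts' 2-month outcomes out of the main estimate.

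The between-arm result is open to bias if dropout differs by arm in rate or mechanism. It is not shown to be biased, and neither the direction nor the size can be read from the protocol. The within-group improvements are exposed even without a difference between arms. All the sizes in the working depend on the assumed correlations and dropout strength. At the plan's own attrition the bias is modest, below half a standard error; it grows if 6-month loss exceeds the 12% taken from shorter studies.

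The change is worth making because the data that would reduce the problem are already collected. It is a recommended improvement to the analysis, not a flaw that invalidates the trial.

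**What to change.** In the Data Analysis section:

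1. Make the primary analysis one that includes all randomised participants with the data they gave. Use either (a) a likelihood-based repeated-measures model of the 2- and 6-month outcomes adjusted for baseline, with a logistic mixed model or equivalent for the binary main outcomes, or (b) multiple imputation separately by arm, with the baseline and 2-month values in the imputation model, followed by the 6-month comparison.
2. Take the within-group changes from the same analysis.
3. Report the 6-month completer ANCOVA as supportive.
4. Add a delta-adjusted imputation as the sensitivity analysis, with leavers worse than predicted by, say, 0 to 0.5 SD, varied separately by arm, and report the shift at which the conclusion changes. This is needed because the 2-month scores remove the bias only when they explain dropout.
5. State how participants without a baseline questionnaire are handled, since Recruitment and Participants places allocation before it.

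Cost: revised wording and a little more programming. N stays at 120 and no new data are needed. In a separate simulation of 4,000 trials (60 per arm, correlations 0.6, 0.5 and 0.7 assumed, 12% random v about 18% selective dropout), using the 2-month score lost no precision: empirical SE 0.170 against 0.172 for the completer ANCOVA.

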### Primary Outcome Measures: Depression, Physical Activity, and Dietary Intake

As the main outcomes, we will examine differences between the 2 groups in the proportion of participants who are:

classified as *nondepressed* at baseline, post program, and follow-up (based on a PHQ-9 score of <6) [55,56],achieving physical activity guidelines of ≥150 minutes of physical activity per week [52] at baseline, post program, and follow-up, orachieving healthy dietary guidelines of DQT scores >60% [62] at baseline, post program, and follow-up.

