### Sample Size and Power

Our sample size is based on a systematic review of telehealth-based cardiac rehabilitation [28] on lifestyle behaviors, health outcomes, and quality of life, where the effect sizes on promoting healthy lifestyle ranged from 0.42 to 1.29. Taking a conservative approach, we expect a medium effect size of 0.55. Allowing for 80% power and a significance threshold of .05, the estimated sample size is 120 (60 per arm), which takes into consideration an expected attrition rate of 12% based on prior studies with similar posttest time points of 2-4 months [31,51].

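### The primary outcomes are proportions, but the stated model (ANCOVA with Hedges g) suits scores and the 0.55 effect size has no metric, so 80% power is not shown for the stated endpoints

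*Protocol article*

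**What the plan says.** Three sections of the protocol article bear on this.

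- **Primary Outcome Measures: Depression, Physical Activity, and Dietary Intake** (in the analysis part) sets the endpoint: "As the main outcomes, we will examine differences between the 2 groups in the proportion of participants who are" in one of three target states. These are nondepressed ("based on a PHQ-9 score of <6"), "achieving physical activity guidelines of ≥150 minutes of physical activity per week", and a DQT score above 60%. All three are binary.
- **Data Analysis** sets the model: "The effect of the intervention on the primary and secondary outcomes at 6 months will be assessed using analysis of covariance (ANCOVA) models", with the baseline value as covariate and arm as factor. The summary is "The treatment effect, its effect size (Hedge g), and 95% CIs for the treatment effect". No method for a binary outcome is named for the primary outcomes.
- **Sample Size and Power** sets the size. It cites a review "where the effect sizes on promoting healthy lifestyle ranged from 0.42 to 1.29", then says "Taking a conservative approach, we expect a medium effect size of 0.55", and concludes "Allowing for 80% power and a significance threshold of .05, the estimated sample size is 120 (60 per arm", allowing for 12% attrition. It does not name the metric of the 0.55, the outcome it applies to, or an expected proportion in either arm.

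The earlier descriptions of the PHQ-9, the activity survey and the DQT give both a score or quantity and a cut-off, so they do not settle which is primary.

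**The concern.** The article fixes both the endpoint and the model, and the two do not match. This is therefore more than detail left to an analysis plan. Hedges g does not suit a yes/no outcome. An analyst following the text must either fit the linear model to 0/1 data and report a g of unclear meaning, or switch to the scores and so change the endpoint. For three listed outcomes, that choice could be made after the data are seen.

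The sample size has the same gap. Cutting a score at a threshold discards information, so a shift detectable on the score with 80% power is generally detectable with less power as a proportion. The primary comparison is meant to decide how the program is rolled out. A null result would be read against a power figure that the article does not tie to these endpoints.

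**Working it through.** **1. Reproduce the stated size.** Inputs from Sample Size and Power: effect 0.55, power 80%, significance .05 (sidedness not stated; two-sided assumed), attrition 12%.

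For two means, n per arm = 2(z₀.₉₇₅ + z₀.₈₀)² / d² = 2(1.960 + 0.842)² / 0.55² = 51.9, so 52. Then 52 / 0.88 = 59.1, so 60 per arm and 120 in total, an exact match. The t-test version gives 52.9, so 53 per arm, and 53 / 0.88 = 60.2. A one-sided test gives 41 per arm and 94 in total after attrition, which does not match. Evaluable per arm: 60 × 0.88 = 52.8, about 53.

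**2. Same shift, dichotomised.** Assume 0.55 is a standardised mean difference on a normal score and the self-directed arm has proportion p₁ on target. The article gives no p₁, so a range is used.

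- p₂ = Φ(Φ⁻¹(p₁) + 0.55)
- power = Φ{[(p₂ − p₁) − 1.96√(2p̄(1 − p̄)/53)] / √([p₁(1 − p₁) + p₂(1 − p₂)]/53)}, where p̄ is the mean of p₁ and p₂

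Example, p₁ = 0.50: p₂ = 0.709 and p̄ = 0.604. The numerator is 0.209 − 0.186 = 0.023 and the denominator 0.093, so power = Φ(0.24) ≈ 60%.

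| Self-directed | Supported | Unadjusted power, 53 per arm | Completers per arm for 80% |
|---|---|---|---|
| 20% | 38.5% | 55.5% | 94 |
| 30% | 51.0% | 59.9% | 85 |
| 40% | 61.7% | 60.9% | 83 |
| 50% | 70.9% | 59.6% | 85 |
| 60% | 78.9% | 56.2% | 92 |
| 70% | 85.9% | 50.4% | 107 |
| 80% | 91.8% | 41.4% | 136 |

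A logistic rather than normal score (odds ratio exp(0.55π/√3) = 2.71) is somewhat kinder: 70%, 69%, 63% and 53% at control rates of 30%, 50%, 60% and 70%.

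**3. With baseline adjustment.** Simulating the 0.55 SD shift with 53 per arm and a logistic model adjusted for the baseline score gives roughly 54–76% power (assumed score correlation 0.5–0.7, control rates 30–70%). These figures can move by a few points with the simulation and the test used. For comparison, ANCOVA on the score itself gives about 90% at a correlation of 0.5.

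**4. The other reading: 0.55 as Cohen h.** Here h = 2·arcsin√p₂ − 2·arcsin√p₁, and n = 2(1.960 + 0.842)² / h² is again 51.9 per arm. So p₂ = sin²(arcsin√p₁ + 0.275): 30% vs 57%, 50% vs 76%, 70% vs 91%. Power at 53 per arm is 79–81% for control rates 30–70%, falling to about 76% at 80%.

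**5. Detectable difference, 80% power, 53 per arm, unadjusted.** 20% vs 45.3%, 30% vs 56.7%, 40% vs 66.8%, 50% vs 76.0%, 60% vs 84.1%, 70% vs 91.3%. These are differences of about 21 to 27 percentage points.

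**The case against.** The strongest reply is that the article never calls 0.55 a standardised mean difference. Step 4 shows that Cohen h fits 60 per arm about as well and keeps about 80% power for proportions. This stands. A reader might infer that the size can only come from a comparison of means, or that the trial is simply underpowered. The document supports neither. What remains is that Hedges g in Data Analysis makes the mean-difference reading the likely one. The Cohen h reading also needs gains of 21–27 points from adding two telephone sessions to a program that both arms receive, and no such gain is stated.

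Second, baseline adjustment recovers power, so quoting only unadjusted figures would overstate the loss. This also stands, and is why both ranges are given. A linear approximation with correlation 0.6 reaches 80–82% at control rates 30–50%. That 0.6 is between the yes/no variables, however, and at a median split it corresponds to sin(0.6 × π/2) ≈ 0.81 on the underlying score.

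Third, a linear model on 0/1 data in a randomised trial does estimate a risk difference, so ANCOVA would not be invalid. The clearer misfit is Hedges g. The ANCOVA sentence also covers all outcomes generically, and model detail often sits in an analysis plan. Even so, the article names one model and one effect measure for the primary outcomes, and the effect measure does not fit them.

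Two further inferences should not be drawn. Participants already on target at baseline are not lost to the comparison: they can relapse less in one arm, and their share is already in the control rate. Listing baseline among the timepoints does not specify a significance test at baseline, and the within-arm hypothesis needs baseline proportions.

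**Conclusion.** The point holds as a mismatch between endpoint, model and power basis, not as an arithmetic error. The 80% power is not shown for the three proportions.

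- If 0.55 is a standardised mean difference, power is about 41–61% unadjusted and roughly 54–76% with baseline adjustment. Reaching 80% unadjusted would take 83 to 136 completers per arm, or about 190 to 310 in total after 12% attrition.
- If 0.55 is Cohen h, about 80% is right, but only for differences of about 21–27 points.

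The control rates, the normal score and the baseline correlations are assumptions, because the article supplies none of them. The flat statement that 80% power is not delivered goes further than the document allows.

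**What to change.** Reconcile Sample Size and Power, Data Analysis, and the primary outcome section before unblinding, and state the metric of the 0.55. There are two routes.

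**(a) Keep the proportions primary.** For these outcomes, replace ANCOVA and Hedges g with a logistic model adjusted for the baseline score, reported as a risk difference with 95% CI. Replace the 80% statement with the detectable difference at 53 per arm (about 21–27 percentage points, unadjusted) or with a power range and its assumptions. The endpoint does not change; the cost is a less favourable stated power.

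**(b) If the scores were the intended primary endpoints, say so.** Keep ANCOVA, Hedges g and N = 120, and make the proportions supportive. The cost is more than wording. Enrolment had closed with 122 participants, so this is a documented change of primary endpoint and needs a dated registry amendment before unblinding.

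Neither route needs new data.

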## Methods

### Study Design

This project uses a 2-armed RCT design, with participants who register to be involved in the trial being randomly allocated to one of two arms: either “self-directed” completion of the *Back on Track* program or “supported” completion of the *Back on Track* program. The self-directed arm involves participants completing the web-based *Back on Track* program at their own pace without assistance. The supported arm involves the addition of 2 telephone sessions with a trained lifestyle counselor. The telephone sessions are protocol driven, with a written manual developed by a health psychologist.

Measures are assessed at three timepoints across the study: a baseline questionnaire is completed prior to participants receiving access to the web-based program, a postprogram questionnaire at the conclusion of the web-based program access (2 months after baseline), and a follow-up questionnaire 4 months later (6 months after baseline). Figure 1 shows a flowchart of the study design and the participant numbers.

An RCT design was chosen for this trial to accurately compare outcomes for the 2 modes of delivery of the web-based *Back on Track* program, either self-directed or supported. By comparing outcomes for participants in the 2 groups, we will be able to determine whether the supported approach provides benefits over and above the self-directed use of the web-based *Back on Track* program. The result will then inform the optimal form of delivery of the *Back on Track* program for future rollout to people with CHD across Australia.

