In all cases of recruitment, both direct and indirect, potential participants are directed to the ACHH website for detailed information about the study and for instructions on how to register on the internet. Screening for eligibility is undertaken at the time of participant registration via the ACHH website using a set of brief screening questions; specifically, participants are asked to provide their name and contact details, type, and date of cardiac event and to confirm that they are able to read and understand English and that they have access to the internet and a computer or tablet device. All participants are asked to read, sign, and return the participant information and consent form (PICF) after registration and prior to randomization and being given program access. The PICF is emailed to participants via the secure web-based data management and survey program, Research Electronic Data Capture (REDCap), which they sign and return electronically to ACHH.

Once registered, participants are randomly allocated to either the self-directed or the supported arm of the trial using an independent and automatic random allocation numbering system. The person undertaking the random allocation is blind to group and participant details. All participants are then asked to complete the web-based baseline questionnaire, also disseminated using REDCap. The link to questionnaires is emailed to participants at each timepoint. Access to the *Back on Track* program is granted to participants for a 2-month period after they complete the baseline questionnaire.

Participants are asked to recomplete the main outcome measures again post program (2 months after initial access to the program) and at 4-month follow-up (6 months after program access). Again, the REDCap survey link is emailed to participants.

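### Baseline is listed as a timepoint for the main between-arm comparisons, although it cannot show an intervention effect, while the 2-month comparison and the proportions have no stated baseline adjustment

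*Protocol article*

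**What the plan says.** The section Primary Outcome Measures: Depression, Physical Activity, and Dietary Intake introduces the main outcomes with "we will examine differences between the 2 groups in the proportion of participants who are" and then lists three binary states. Each carries the same three timepoints. For depression the text reads "at baseline, post program, and follow-up (based on a PHQ-9 score of <6", and for activity "physical activity per week [52] at baseline, post program, and follow-up". The diet item repeats the formula.

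The order of events is given elsewhere in the article:

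- Study Design: "a baseline questionnaire is completed prior to participants receiving access to the web-based program".
- Recruitment and Participants: after random allocation, "All participants are then asked to complete the web-based baseline questionnaire". Access to the "program is granted to participants for a 2-month period after they complete the baseline questionnaire".
- Additional Telephone Sessions for the Supported Group: the first call comes about 1-2 weeks after enrollment.

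On analysis, the Data Analysis section states "All statistical analyses will be performed on an intention-to-treat (ITT) basis", with a .05 threshold for the primary outcome and .01 for secondary outcomes. It assesses the effect on primary and secondary outcomes at 6 months by ANCOVA, with the baseline value as covariate, and reports Hedges g. The Objectives hypothesize that the supported arm improves more than the self-directed arm at both 2 and 6 months.

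**The concern.** A main outcome should be able to respond to the intervention. A between-arm difference measured before the program opens and before any counseling call cannot. Yet the section on the main outcomes puts it on the same footing as the 2- and 6-month differences.

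Two things are at stake. First, a significant baseline difference would appear among the main results with no useful interpretation. Second, the same section treats baseline as one more column to compare and names no adjustment for it. The only adjusted model in the article is the 6-month ANCOVA, which does not cover 2 months and which, with Hedges g, is built for scores and not for proportions. A 2-month comparison run as that section is written would leave unused the baseline status that every participant is asked to provide.

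**Working it through.** **1. The plan's own figure.** Inputs from Sample Size and Power: effect size 0.55, power 80%, alpha .05 (taken as two-sided), attrition 12%.

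n per arm = 2 × (1.96 + 0.842)² / 0.55² = 51.9, so 52. Then 52 / 0.88 = 59.1, so 60 per arm and 120 in total.

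The stated 120 is reproduced. The baseline comparisons play no part in it.

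**2. Count of main comparisons.** 3 outcomes × 3 timepoints = 9. At baseline: 3 × 1 = 3, so 3/9 = 33%. Without baseline: 3 × 2 = 6.

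**3. Can the baseline three respond to treatment?** The order is allocation, baseline questionnaire, program access, first call. Both components of the intervention come after the measurement, so they cannot.

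**4. What role does baseline have at each timepoint?**

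- 6 months, Data Analysis: covariate in an ANCOVA.
- 6 months, main-outcome section: difference in proportions, no model or adjustment named.
- 2 months, main-outcome section: difference in proportions, no model or adjustment named. The Data Analysis section gives no adjusted model for this timepoint.
- Baseline, main-outcome section: compared between arms.

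Baseline is therefore both a covariate and a compared outcome, and the two sections are not reconciled.

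**5. Chance results if the three baseline differences were tested.** At .05 each, assuming independence and no baseline difference beyond chance: 1 − 0.95³ = 0.143.

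**6. Size of a chance gap.** With 60 per arm and an assumed 50% to 65% in the favorable state, SD = √(2p(1 − p)/60):

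- p = 0.50: 0.091, and 1.96 × 0.091 = 0.179.
- p = 0.65: 0.087, and 1.96 × 0.087 = 0.171.

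A typical (one-SD) gap is about 9 percentage points. Only gaps above about 17-18 points would reach P<.05, so a non-significant baseline test says little about balance.

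**7. What an unadjusted later comparison carries.** With an assumed baseline-to-later correlation (phi) of 0.3 to 0.5 and similar proportions at both times, the carry-over is phi × gap: 0.3 × 9 = 2.7 points and 0.5 × 9 = 4.5 points.

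**8. What adjustment gains.** On the risk-difference scale, the variance of the arm difference falls to roughly 1 − phi²: 1 − 0.3² = 0.91 and 1 − 0.5² = 0.75. That is a reduction of 9% to 25% under the same assumption.

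**The case against.** The strongest reply is that the phrase only repeats the measurement schedule. The Measures section names the same three occasions, the Objectives hypothesize a between-arm difference only at 2 and 6 months, and the main-outcome section names no test. On that reading the authors mean to show proportions at each occasion with baseline as reference. This is possible, and it means that baseline significance tests are an inference from the general .05 rule and not a stated plan. But the wording is attached to the main between-arm differences three times, and nothing marks baseline as descriptive.

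Three stronger readings are tempting, and the article does not support them:

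- *Baseline is an outcome instead of a covariate.* The Data Analysis section makes it a covariate for the primary outcomes at 6 months.
- *A baseline gap can only be chance.* The questionnaire follows allocation. Unequal completion, or knowledge of the arm if it had been disclosed (the article does not say), could also produce one.
- *The follow-up comparison is biased.* Under randomization a chance imbalance is already covered by the standard error, and the type I error rate holds. What is lost without adjustment is precision.

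It is also fair to say that a significant baseline difference could not be claimed as efficacy, so the 14% is not a risk of falsely declaring benefit. Model detail is often left to an analysis plan, but the timepoints of the main comparisons are stated here and stated badly.

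**Conclusion.** The point holds as a matter of wording and efficiency. Three of the nine listed main comparisons (33%) cannot measure an intervention effect. Baseline has two unreconciled roles, and neither the 2-month comparison nor the proportions have a stated baseline adjustment.

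The sizes are modest and partly assumed. The 14% requires that all three baseline differences are tested and independent. The 9-point typical gap, the 2.7-4.5 points carried over and the 9-25% variance reduction rest on assumed proportions of 50-65% and phi of 0.3-0.5, which the article does not give.

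A reader might infer that the 6-month effect estimate is compromised. It is not, because its ANCOVA already adjusts for baseline by prior specification. The sample size is unaffected.

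**What to change.** In the main-outcome section, limit the between-arm comparisons to post program (2 months) and follow-up (6 months). Adjust each for the participant's baseline value or status. For the proportions, one option is a binary-outcome model with arm and baseline status. Amend the Data Analysis section to match, so that it says which model serves the scores and which the proportions, and covers both timepoints.

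Report baseline proportions by arm descriptively, without P values, and state that an observed baseline difference will not decide whether to adjust.

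The cost is a few sentences of analysis wording and three P values no longer reported. Baseline status is already collected, so no new data are needed and N=120 stays as it is.
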